### Data and safety monitoring board

An independent data and safety monitoring board (DSMB) will monitor patient safety and the study conduct. The DSMB will hold regular meetings to ensure there is no imbalance in endpoints, with focus on recurrent ischemic strokes and intracerebral haemorrhages. In case of revealed harm or overwhelming superiority associated with one of the treatment arms, the DSMB will recommend premature termination of the study.

### Sample size estimates

To address paucity of data on early stroke recurrence rate in Sweden, we performed a retrospective, medical record review study (the Pre-TIMING study) to investigate the stroke recurrence rate in patients with acute ischemic stroke and AF during the index hospitalisation. This observational study included all consecutive patients with acute ischemic stroke and AF registered in The Swedish Stroke Register during 2014 at Skåne University Hospital, Lund and Uppsala University Hospital. The results of this study revealed 4% recurrent ischemic stroke and 3% symptomatic ICH during the index hospitalisation (mean = 16 days) and 4% all-cause mortality at 90 days in patients with OAC therapy [29].

The sample size calculation in TIMING is based on findings from the Pre-TIMING study [29]. The proportion of events of the primary composite variable at 90 days is assumed to be 12% in both treatment regimes. The non-inferiority margin is set to be 0.03. The selection of non-inferiority margin is based on magnitudes of commonly observed and meaningful relative and absolute risk reductions in a wide range of secondary stroke preventive trials [30]. Based on these assumptions, a sample size of 1451 patients per group would be sufficient to test the primary hypothesis (non-inferiority) with a power of 80% using a significance level of 5%. Although there is no loss to follow-up in the National Board of Health registers, we conservatively set the sample size to 3000 patients.

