### Statistical analyses

The primary composite outcome of new ischemic stroke or symptomatic ICH or all-cause mortality within 90 days will be analysed using an ordinary z-test for proportions. The hypothesis to be tested is if early start of NOAC treatment is non-inferior to delayed start of treatment. Non-inferiority will be tested by comparing the lower limit of the two-sided confidence limit for the difference in proportions of events for the two treatment regimens to the suggested delta value (i.e. the non-inferiority margin). If the data support the non-inferiority claim, the hypothesis of superiority will also be tested; a testing strategy supported by current guidelines [31]. A Cox proportional hazard model will be used as a sensitivity analysis. Differences between treatment regimens for the individual components of the primary composite variable will be tested as secondary outcomes. Subgroup analyses will be performed based on age, sex and stroke severity.

The Modified intention-to-treat population is the primary efficacy and safety dataset and will consist of all randomised individuals who receive at least one dose of NOAC treatment during the treatment period (Modified intention-to-treat population). Participants will be presented in the treatment start group to which they were randomised (even if the treatment started at a time point different than what was decided by the randomisation). The Per protocol population will be a subset of the Modified intention-to-treat population. All data points after a relevant protocol deviation will be excluded from this dataset. This dataset will be used for sensitivity analyses of the primary efficacy endpoint if > 10% of participants in any treatment group have relevant protocol deviations.

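### The 1451 per group gives 80% power only for an unstated one-sided 5% test; if the two-sided interval is a 95% interval, power is about 70–72%

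*Protocol article*

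**What the plan says.** Under Sample size estimates, the Protocol article gives these design inputs:

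- Event rate: "The proportion of events of the primary composite variable at 90 days is assumed to be 12% in both treatment regimes".
- Margin: "The non-inferiority margin is set to be 0.03".
- Size and power: "a sample size of 1451 patients per group would be sufficient to test the primary hypothesis (non-inferiority) with a power of 80" per cent, "using a significance level of 5" per cent. The sidedness of the 5% is not given.
- The total is then set at 3000, that is 1500 per group under 1:1 randomisation.

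Under Statistical analyses, the primary outcome is compared by a z-test for proportions. Non-inferiority is decided by "comparing the lower limit of the two-sided confidence limit for the difference in proportions of events for the two treatment regimens" and setting that limit against the margin. The confidence level is not given. If non-inferiority is supported, superiority is tested next, and no level is given for that step either.

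**The concern.** The 5% in the sample size section is the only error level in the article, and the decision rule rests on an interval described as two-sided. Many readers will put these together as a 95% interval. One limit of a 95% interval carries a one-sided error of 2.5%, whereas the sample size appears to have been calculated at one-sided 5%.

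Two things depend on which is meant: the power the trial can claim, and how large an observed excess of events with early start still counts as non-inferior. The trial is open-label, so the threshold for the primary conclusion should be fixed in writing and not left to be inferred.

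**Working it through.** **Inputs (Sample size estimates):** event rate 0.12 in both arms, so a true difference of 0; margin 0.03; power 80%; 1451 per group; planned total 3000.

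**Formula.** For a z-test with unpooled variance, n per group = (z_a + z_b)² × 2 × 0.12 × 0.88 / 0.03², with z_b = 0.8416 for 80% power and 2 × 0.12 × 0.88 = 0.2112.

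**Step 1: reproduce the plan's figure.**
- One-sided 5% (z_a = 1.645): n = 1450.8, rounded up to **1451**. This matches exactly.
- One-sided 2.5% (z_a = 1.960): n = 1841.9, rounded up to **1842**, or 3684 in total.

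Other formulas do not give 1451. Farrington-Manning null variance gives 1460 (one-sided 5%) or 1854 (one-sided 2.5%). A pooled test of 12% against 15% gives 1604 one-sided or 2036 two-sided, and of 12% against 9% gives 1291 or 1638. Continuity correction of the pooled tests gives 1670 and 2102, and 1356 and 1704. The sample size was therefore almost certainly built on one-sided 5%.

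**Step 2: power under each reading.** Power = Φ(0.03/SE − z_a), with SE = √(0.2112/n). The SE is 0.01207 at 1451 and 0.01187 at 1500 per group.

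| Interval used for non-inferiority | One-sided error | Power at 1451 | Power at 1500 | n per group for 80% |
|---|---|---|---|---|
| Two-sided 90% | 5% | 80.0% | 81.1% | 1451 |
| Two-sided 95% | 2.5% | 70.1% | 71.5% | 1842 |

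A simulation of the Wald interval with 1,000,000 replicates agrees: 80.0% and 81.2% for the 90% interval, 70.2% and 71.6% for the 95% interval. At 1500 per group, the chance of missing true non-inferiority is about 19% on the first reading and about 28% on the second.

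**Step 3: effect on the decision.** Take 1500 per group and hold the SE at 0.01187. Write the difference as early minus delayed, so that the upper limit is compared with 0.03. This is the same as the lower limit of delayed minus early compared with −0.03. Non-inferiority is then declared if the observed excess is below
- 0.03 − 1.645 × 0.01187 = 0.0105 with a 90% interval (about 15.7 events in 1500);
- 0.03 − 1.960 × 0.01187 = 0.0067 with a 95% interval (about 10.1 events in 1500).

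An excess of about 11 to 15 events in the early arm would pass under one reading and fail under the other.

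**The case against.** The strongest reply is that nothing in the article is contradictory. The 1451 follows exactly from the stated inputs. A non-inferiority decision uses one limit, so it is one-sided even when the interval is two-sided, and a two-sided 90% interval has exactly the one-sided 5% error on which 1451 is built. The 95% figure appears nowhere in the article. One-sided 5% is a permissible design choice if declared. The confidence level may also be given in the full protocol (version 2.0) or in an analysis plan, neither of which is shown.

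Much of this stands, and it rules out several stronger conclusions that a reader might draw:

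- *That 1451 is a calculation error.* It is not; it reproduces exactly.
- *That the two sections state different thresholds.* They do not, because the analysis section states no level. A 90% interval would reconcile them at 80–81% power.
- *That superiority will be tested at two-sided 10%.* This would follow only if a 90% interval were reused for superiority, and the article does not say that it will be.

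What the reply does not remove is that the article itself publishes a level, a power and a sample size that fit together on only one unstated reading. A full protocol or analysis plan that specifies 95% would make the published 80% wrong. One that specifies 90% would leave the bare 5% beside a two-sided interval open to misreading.

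**Conclusion.** The concern holds as an ambiguity about the level of the primary test that affects the stated power. It is not an arithmetic error. The 80% (81% at 1500 per group) is right only if non-inferiority is judged at one-sided 5%, that is by a two-sided 90% interval. On the 95% reading, which the wording invites, power is about 70% at 1451 and 72% at 1500 per group, and the increase to 3000 patients does not restore 80%.

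The 72% is conditional on that reading and is not an established property of the trial. All figures assume 12% events in both arms, no true difference, an unpooled z-test, and 1500 per group actually analysed.

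The point should still be settled, because it governs the primary decision rule and a figure on which the trial relies, and because settling it is cheap.

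**What to change.** State the one-sided error and the interval level, in the same terms, under both Sample size estimates and Statistical analyses. Either of two forms is coherent:

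1. Judge non-inferiority by the two-sided 95% interval (one-sided 2.5%), take superiority from the same interval, and restate power as about 72% for 1500 per group.
2. Declare that non-inferiority is tested at one-sided 5% with a two-sided 90% interval, keep the 80% figure, and state that superiority is tested separately at two-sided 5%.

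The choice should be recorded before any comparison of the arms is seen by those who make it. Neither form needs extra patients. The first costs a less favourable stated power; holding 80% at that level would instead take 3684 patients, 684 more than planned. The second costs an openly stated 5% one-sided error for the non-inferiority claim.

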### Statistical analyses

The primary composite outcome of new ischemic stroke or symptomatic ICH or all-cause mortality within 90 days will be analysed using an ordinary z-test for proportions. The hypothesis to be tested is if early start of NOAC treatment is non-inferior to delayed start of treatment. Non-inferiority will be tested by comparing the lower limit of the two-sided confidence limit for the difference in proportions of events for the two treatment regimens to the suggested delta value (i.e. the non-inferiority margin). If the data support the non-inferiority claim, the hypothesis of superiority will also be tested; a testing strategy supported by current guidelines [31]. A Cox proportional hazard model will be used as a sensitivity analysis. Differences between treatment regimens for the individual components of the primary composite variable will be tested as secondary outcomes. Subgroup analyses will be performed based on age, sex and stroke severity.

The Modified intention-to-treat population is the primary efficacy and safety dataset and will consist of all randomised individuals who receive at least one dose of NOAC treatment during the treatment period (Modified intention-to-treat population). Participants will be presented in the treatment start group to which they were randomised (even if the treatment started at a time point different than what was decided by the randomisation). The Per protocol population will be a subset of the Modified intention-to-treat population. All data points after a relevant protocol deviation will be excluded from this dataset. This dataset will be used for sensitivity analyses of the primary efficacy endpoint if > 10% of participants in any treatment group have relevant protocol deviations.

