## Methods

### Design

The prospective TIMING study is a national, investigator-led, registry-based, multicentre, open-label, non-inferiority, RCT. The intervention in this study is not the pharmacological agents (i.e. apixaban, dabigatran, edoxaban and rivaroxaban) per se, but rather the actual timing of treatment initiation. This registry-based RCT (R-RCT) will use the Swedish Stroke Register for enrolment, randomisation and follow-up [1]. Additional data will be retrieved through record linkage with mandatory national registers. An overview of the study is presented in Fig. 1 and a SPIRIT Checklist is included as Additional file 1.

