### Randomisation

Eligible patients will be randomised by the treating physician at the patient’s local hospital, within 72 h from stroke onset. The choice of NOAC (i.e. apixaban, dabigatran, edoxaban or rivaroxaban) is at the discretion of the treating physician as all four are available and reimbursed in Sweden. If eligible and willing to participate, the patient will be given a study specific ID and thereafter be randomly allocated, equal in each study arm, to early (≤ 4 days) or delayed (≥ 5–10 days) start of NOAC by a central computer within the Swedish Stroke Register/R-RCT infrastructure.

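### The primary dataset keeps only patients who receive a NOAC dose, so events in patients who never start are lost, and the delayed arm has longer to lose them

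*Protocol article*

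**What the plan says.** The Statistical analyses section of the protocol article states: "The Modified intention-to-treat population is the primary efficacy and safety dataset". That set "will consist of all randomised individuals who receive at least one dose of NOAC treatment during the treatment period". Within it, "Participants will be presented in the treatment start group to which they were randomised", whatever the actual start day. One other set is named: "The Per protocol population will be a subset of the Modified intention-to-treat population".

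The Design section explains that the intervention is not the drug "but rather the actual timing of treatment initiation". Under Randomisation, patients are allocated "within 72 h from stroke onset" to "early (≤ 4 days) or delayed (≥ 5–10 days) start of NOAC". The Abstract counts the 90-day primary outcome from randomisation, so the time before the first dose is part of follow-up.

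**The concern.** A one-dose rule does little harm when both arms are dosed promptly under the same conditions. Here the two arms differ by design in how long a patient waits for the first dose, so whether a dose is ever given is settled after randomisation, over an at-risk period that the allocation sets.

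A patient who dies while waiting cannot enter the primary set. A patient who bleeds while waiting may never be started; Table 1 lists ongoing bleeding as a contraindication to NOAC. Either way the patient and the event leave together. Analysing the remaining patients as allocated does not bring them back, and neither does the per protocol set, which is nested inside the same population.

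Events that happen during the wait are part of the effect of waiting. Losing some of them, more often from the delayed arm, lowers that arm's observed risk. This touches the non-inferiority test, the superiority test that follows it, the component comparisons and the safety comparison.

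**Working it through.** **1. The plan's own sample size.** Inputs from Sample size estimates: 12% in both arms, margin 0.03, power 80%, level 5%.

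n per group = (z_alpha + z_beta)² × 2 × 0.12 × 0.88 / 0.03²

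- One-sided 5%: (1.645 + 0.842)² × 0.2112 / 0.0009 = 1451, which matches.
- One-sided 2.5%: 1842, which does not match.

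Power below is therefore given at one-sided 5%. With all 3000 randomised patients analysed (1500 per arm), the standard error is √(2 × 0.12 × 0.88 / 1500) = 0.011866. Power is Φ(0.03/0.011866 − 1.645) = 81%, and the expected difference is 0 when the true risks are equal.

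**2. Time at risk before the first dose (assumed).** Randomisation is spread evenly over days 0.5–3, early start over days 1.5–4 and delayed start over days 5–10.

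- Delayed: mean wait 7.5 − 1.75 = 5.75 days.
- Early: mean wait about 1.1 days, counting a start day drawn before randomisation as no wait. The longest early wait is 4 − 0.5 = 3.5 days.

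**3. Daily hazards.** These come from the Pre-TIMING figures: "The results of this study revealed 4% recurrent ischemic stroke and 3% symptomatic ICH during the index hospitalisation" (mean 16 days), and 4% mortality at 90 days. Hazards are assumed even over those periods.

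- Death: 4%/90 = 0.0444% per day
- Symptomatic ICH: 3%/16 = 0.1875% per day
- Recurrent ischaemic stroke: 4%/16 = 0.25% per day

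**4. Shift.** Let x be the share of an arm that has an event before the first dose and never starts, so x = hazard × mean wait. The true risk is 12% in both arms. Risk in the dosed set is (0.12 − x)/(1 − x). Power is Φ((0.03 − shift)/0.011866 − 1.645).

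| Pre-dose patients who never start | Hazard, %/day | x early, % | x delayed, % | Risk early, % | Risk delayed, % | Shift, points | Power |
|---|---|---|---|---|---|---|---|
| Deaths only | 0.0444 | 0.05 | 0.26 | 11.96 | 11.77 | 0.18 | 77% |
| Plus half of ICH | 0.1382 | 0.15 | 0.79 | 11.87 | 11.30 | 0.57 | 66% |
| Plus all ICH | 0.2319 | 0.26 | 1.33 | 11.77 | 10.81 | 0.96 | 53% |
| Plus all recurrent strokes | 0.4819 | 0.53 | 2.77 | 11.53 | 9.49 | 2.04 | 20% |

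Simulation of the same scenarios agrees within about two percentage points of power: 75%, 65%, 51% and 19%, with a top shift of about 2.1 points.

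**5. What makes it smaller.**

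- Shorter extra wait: with mean waits of 2.5 and 4.5 days and half of pre-dose ICH patients never starting, x is 0.35% and 0.62%, the shift is about 0.25 points and power about 75%.
- Event-free never-starters: in the all-ICH row, also dropping 1% of early and 3% of delayed patients without an event gives (0.12 − 0.0026)/(1 − 0.0026 − 0.01) = 11.89% against (0.12 − 0.0133)/(1 − 0.0133 − 0.03) = 11.15%. The shift falls from 0.96 to about 0.74 points.
- Equal losses in both arms give no shift.

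**6. False signal for delay.** At the 0.96-point shift, the chance of a nominal two-sided 5% result favouring delay is Φ(0.0096/0.011866 − 1.96), about 13% instead of 2.5%.

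**The case against.** Several counter-arguments have force.

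- **Only never-dosed patients leave.** A reader might infer that the rule strips out every event in the delayed arm's waiting period. It does not. A patient with a recurrent stroke or bleed who later starts NOAC stays in the allocated arm with the event counted. Early-arm patients can also be lost, over a wait that may reach about 3.5 days.
- **The size is not fixed by the protocol.** A reader might take a shift of one point as the minimum. That figure assumes that every patient with a pre-dose symptomatic ICH never starts, and the larger one assumes the same of every pre-dose recurrent stroke. The protocol supports neither share, and the Background describes anticoagulation as recommended to prevent recurrence. Nor does it say how much of the 3% ICH came before anticoagulation. The shift could be close to zero.
- **Direction.** A reader might fear a false claim of non-inferiority. By this route the expected bias runs against early start, so the main cost is lost power. A misleading result in favour of delay remains possible.
- **Follow-up.** The statement about no loss to follow-up concerns the National Board of Health registers. Symptomatic ICH needs imaging and a change in stroke score, and sites enter study-specific data. Complete component data for never-treated patients are likely but not stated.
- **Analysis plan.** A supportive analysis of all randomised patients may sit in a statistical analysis plan that is not shown, so its absence here is no defect.

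These points limit the wording and the size. They do not change the fact that the stated primary set is defined by an event after randomisation whose at-risk period depends on the arm.

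**Conclusion.** The primary population is wrong as written for a trial of timing. The early-minus-delayed difference is expected to shift upwards by about 0.2 points if only pre-dose deaths are lost, and by up to about 2.0 to 2.1 points if every pre-dose death, ICH and recurrent stroke leads to no start. The intermediate cases are about 0.6 and 1.0 points. The upper end uses about two thirds of the 3-point margin.

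These figures assume equal true risks of 12%, even hazards from the Pre-TIMING rates with 4% mortality, and mean waits of about 5.8 and 1.1 days. The share who never start is an assumption throughout. Shorter extra waits reduce the shift, and event-free never-starters partly offset it.

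**What to change.** Define the primary efficacy and safety dataset as all randomised patients, analysed by allocated arm, with events counted from randomisation whether or not NOAC was started. Keep the set with at least one dose as a labelled sensitivity set, and per protocol as supportive.

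The cost is a change of wording in the protocol and analysis plan. The planned 3000 patients stand, because power with everyone analysed is the 81% shown above. The Design section already places follow-up in the Swedish Stroke Register, so starting NOAC is not a condition for collecting outcomes. It is worth adding a sentence that sites complete the stroke and ICH data for never-treated patients too. The small downside is that never-treated patients slightly dilute the contrast between the arms.

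### The per-protocol check on the non-inferiority result is run only above 10% deviations in an arm, although smaller amounts of crossover already favour the claim

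*Protocol article*

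**What the plan says.** The Design section describes the trial as "investigator-led, registry-based, multicentre, open-label, non-inferiority, RCT" and says that the thing being tested is when treatment starts, not which drug is used. The Randomisation section sets two adjoining windows, up to day 4 and from day 5 to day 10.

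Under Statistical analyses, the primary set is a modified intention-to-treat population: randomised patients who took NOAC at least once. They are kept in their allocated group "even if the treatment started at a time point different than what was decided by the randomisation". The per-protocol population is a subset of this, and its use is conditional: "This dataset will be used for sensitivity analyses of the primary efficacy endpoint if" more than 10% "of participants in any treatment group have relevant protocol deviations". The only other sensitivity analysis named for the primary outcome is a Cox model. No different population and no handling of timing deviations is stated for it.

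Under Sample size estimates, the event proportion "is assumed to be 12% in both treatment regimes". On the margin, the text reads: "The non-inferiority margin is set to be 0.03".

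**The concern.** In a superiority trial, analysing patients as randomised usually makes the test conservative when some receive the other arm's treatment. In a non-inferiority trial the effect is the reverse: crossover pulls the two event rates together and makes a real excess harder to see. Here a patient who starts in the other arm's window has received something close to the other intervention. The windows adjoin and the allocation is known to the treating physician, so such starts can easily occur.

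A per-protocol analysis is the usual companion check. The plan makes it depend on a count taken after randomisation, with a threshold applied to each arm separately. Deviations of up to 10% in both arms at once therefore leave it switched off. A non-inferiority claim could then rest on a partly diluted comparison with no per-protocol result beside it. How patients near the threshold are classified would decide whether that result exists at all.

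**Working it through.** **Inputs.** From Sample size estimates: event proportion 0.12 in both arms, margin 0.03, power 80%, significance level 5% (sidedness not stated), 1451 per group required, 3000 planned (1500 per arm with equal allocation). Assumed, because the article gives no figure: the fraction of each arm that starts in the other window, and how much of the other arm's risk those patients take on.

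**The plan's own figure.** n = (z_α + z_β)² × 2p(1 − p) / margin².
- One-sided 5%: (1.645 + 0.842)² × 0.2112 / 0.0009 = 1450.8, so 1451. This matches.
- One-sided 2.5%: 1841.9, so 1842. This does not match.

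The planning level is therefore one-sided 5%. Results for one-sided 2.5% are shown as well, because the sidedness is not stated.

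**Model.** Put the truth at the margin: early 0.15, delayed 0.12. Let fractions c_E and c_D of the two arms start in the other window and take on that arm's full risk. Then:
- observed early risk = 0.15 − 0.03 c_E
- observed delayed risk = 0.12 + 0.03 c_D
- expected difference d = 0.03 × (1 − c_E − c_D)
- false non-inferiority rate = Φ((0.03 − d)/SE − z_α), with the unpooled SE at 1500 per arm

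**Worked case, 10% in each arm.** The risks become 0.147 and 0.123, so d = 0.024. SE = √[(0.147 × 0.853 + 0.123 × 0.877)/1500] = 0.01247, and (0.03 − 0.024)/0.01247 = 0.481.
- One-sided 5%: Φ(0.481 − 1.645) = 0.122
- One-sided 2.5%: Φ(0.481 − 1.960) = 0.070

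A simulation of 400,000 trials gave 12.3% and 7.0%.

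**Range of scenarios.** None of these exceeds 10% in an arm, so none triggers the per-protocol analysis.

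| Wrong-window starts | Expected difference | One-sided 5% | One-sided 2.5% |
|---|---|---|---|
| None | 3.0 points | 5.0% | 2.5% |
| 10% in each arm, quarter-strength dilution | 2.85 | 6.4% | 3.3% |
| 10% in each arm, half-strength dilution | 2.7 | 8.0% | 4.3% |
| 5% in each arm, full | 2.7 | 8.0% | 4.3% |
| 10% in one arm only, full | 2.7 | 8.0% | 4.3% |
| 10% in each arm, full | 2.4 | 12.2% | 7.0% |

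Doubling of the error rate needs about 7.6% full crossover in each arm at one-sided 5%, or about 6.5% at one-sided 2.5%. If only one arm deviates it needs about 15% or 13%, which would trigger the analysis. Centring the risks on 12% (13.5% against 10.5%) changes the last row only slightly, to 12.7% and 7.3%.

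**Precision of the per-protocol analysis.** If 10% of each arm is excluded at random, 1350 per arm remain, and SE = √(0.2112/1350) = 0.01251. Power with equal risks is Φ(0.03/0.01251 − 1.645) = 77.4%, against 81.1% at 1500 per arm. At one-sided 2.5% it is 67.0% against 71.5%. The probability that both analyses succeed is about 75% (64% at one-sided 2.5%).

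**The case against.** Several objections have force.

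- **The largest figures are a corner case.** They need deviations near 10% in both arms, nearly all of them true crossovers carrying the other arm's full risk. The article gives no expected deviation rate and does not say what counts as a relevant deviation, a definition that may properly sit in a fuller document. Other kinds of deviation count towards the 10% too, and a delayed-arm patient who starts after day 10 is off schedule without having moved to the early arm.
- **Crossovers that happen easily may dilute little.** Where the windows adjoin, a typical miss may be by a single day. If risk changes gradually with start day, such a patient carries only part of the other arm's risk. The half- and quarter-strength rows of the table reflect this.
- **The dilution is not invisible.** Applying the threshold requires deviations to be counted by arm, so their extent is known either way. The trigger is prespecified and depends on deviations, not on outcomes.
- **Per-protocol analysis is an imperfect detector.** Start time comes after randomisation and may follow early deterioration or an event, so exclusions can bias the result in either direction.

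A reader might infer that the plan more than doubles the false non-inferiority rate, or that it leaves dilution with no check of any kind. The documents do not support either statement: the first holds only under substantial crossover in both arms, and the second overlooks the deviation count. What stands is narrower. Below the threshold, no analysis by treatment actually received is planned, and crossover in that range biases towards the claim. The limits of per-protocol analysis are a reason to interpret it with care beside the primary result. They are not a reason to leave it out.

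**Conclusion.** The point holds as a cheap improvement to the plan, with moderate confidence about its size. The 10% rule is fixed in the text, and in this design the direction of the dilution is towards non-inferiority. Under the assumptions stated (1500 per arm, true 15% against 12%), the false non-inferiority rate can reach about 12.2% instead of 5%, or 7.0% instead of 2.5%, without the per-protocol analysis being triggered. That is the upper end for those risks. Milder and perhaps more realistic scenarios give about 8.0% or 4.3%, or less.

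A reader might also conclude that non-inferiority should be claimed only if both populations agree. That does not follow. It is one convention among several, it lowers the chance of success from about 81% to about 75% (72% to 64% at one-sided 2.5%) even when exclusions are random, and it would give a potentially biased analysis a veto.

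**What to change.** In Statistical analyses, delete the 10% condition. State that the per-protocol non-inferiority analysis of the primary outcome will always be reported against the same 0.03 margin, beside the modified intention-to-treat result, together with the number of wrong-window starts in each arm. Any discordance between the two should be discussed, with the possible bias from post-randomisation exclusions acknowledged. Keep modified intention-to-treat as the primary analysis and do not make agreement a formal condition. The change should be made before outcomes by arm are seen.

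The cost is one extra table and a sentence or two of wording, with no new data or patients. The downside is a second analysis that is slightly less precise, may itself be biased, and may need explaining if it disagrees.
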